## List of Acronyms

|       |                                                             |
|-------|-------------------------------------------------------------|
| ABHS  | Alcohol-Based Hand Sanitizer                                |
| BWH   | Brigham and Women's Hospital                                |
| CDC   | the Centers for Disease Control and Prevention              |
| CETTE | Centros Temporales de Triage y Estabilización               |
| DGRIS | Dirección General de Redes Integradas de Servicios de Salud |
| MOH   | Ministry of Health                                          |
| SESAL | Secretaría de Salud                                         |
| WASH  | Water, sanitation, and hygiene                              |
| WHO   | World Health Organization                                   |

## Project Summary

This protocol describes an evaluation of home-based care (HBC) and hand hygiene practices for COVID-19 patients and their families in Honduras. The World Health Organization (WHO) states that “Home care may be considered for an adult or child with confirmed or suspected COVID-19 when inpatient care is unavailable or unsafe... [or for] patients who have been discharged from hospital.” In Honduras, the Secretaría de Salud (SESAL) has published guidelines for home-based care for patients with confirmed or suspected COVID-19 infection, but there is currently no formal mechanism for monitoring HBC. Evaluation of the use of pulse oximetry to screen COVID-19 patients for hypoxia is needed to determine whether this practice leads to improved patient outcomes for COVID-19 patients receiving HBC. The current project aims to generate operationally relevant data that can be used to guide decisions regarding HBC strategies, and evaluate the feasibility and impact of pulse oximetry for patients receiving HBC. Nested within the HBC study, we will also implement and evaluate a hand hygiene intervention among the project participants, examine intervention acceptability among clinical staff, and assess long-term COVID-19 symptoms. While most persons with COVID-19 recover and return to normal health, some patients can have symptoms that can last for weeks or even months after recovery from acute illness. Given the incidence and changes over time of these symptoms, we will monitor and assess long term symptoms among COVID-19 patients.

### Ethical Review Boards

The study PI is responsible for ensuring that all ethical approval requirements have been met and ethical approval will be obtained from Mass General Brigham IRB and the National Autonomous University of Honduras Faculty of Medical Sciences Bioethics Committee (Comité de Ética en Investigación Biomédica, CEIB).

## Investigators and Institutional Affiliations

### CDC

CDC staff will provide technical support. CDC staff will not collect data or interact with project or study participants. CDC is not engaged in this activity.

## **Funding Source**

This evaluation is funded by the U.S. Centers for Disease Control and Prevention (CDC) under the terms of the cooperative agreement U01GH002238, Reducing the morbidity and mortality due to acute febrile illnesses in Central America and the Dominican Republic.

## Background

As of December 16, 2021, there have been more than 271 million confirmed cases of COVID-19 and 5.3 million deaths worldwide. Secretary General of the United Nations Antonio Guterres has stated that the impact of the COVID-19 pandemic has fallen “disproportionately on the most vulnerable: people living in poverty, the working poor, women and children, persons with disabilities, and other marginalized groups.” In Honduras, as of April 12th, 2021, there had been 378,642 confirmed cases of COVID-19, leading to 10,424 deaths.

While most COVID-19 patients have mild or moderate symptoms, some individuals develop serious or critical signs and symptoms. Persons with marked hypoxia may have normal respiratory rates but later develop severe symptoms or respiratory failure. Timely detection and transfer of persons with hypoxia or other alarm signs and symptoms to a higher level of care is critical.

According to the WHO, “home pulse oximetry is a safe, non-invasive way to assess oxygen saturation in the blood and can support the early identification of low oxygen levels in a patient with initially mild or moderate COVID-19 or silent hypoxia, when a patient does not appear to be short of breath but his or her oxygen levels are lower than expected.” Pulse oximetry can also identify patients for whom it is safe to remain in HBC, thereby reducing unnecessary use of advanced care resources, which are frequently limited. There is currently limited evidence on the impact, feasibility, and acceptability of home-based pulse oximetry in resource-limited settings.

The Honduras SESAL has established an extensive network of COVID-19 triage centers to identify, test and triage potential COVID-19 patients. These centers are known by their Spanish acronym CETTE (Centros Temporales de Triage y Estabilización). Patients that do not require hospitalization are discharged to home. However, there have been difficulties with following and monitoring these patients and at present no mechanism monitors outcomes for these patients. Therefore, this project proposes to establish a framework to provide structured HBC for high-risk patients to include symptom and clinical monitoring, and guidance on when and how to seek additional medical care. Further, at present, the utility of pulse oximetry for monitoring of COVID-19 home-based care patients in lower- and middle-income settings has not been established and although potentially beneficial is not the standard of care in most countries including the US.

Practicing hand hygiene frequently with appropriate technology and technique can mitigate the spread of COVID-19. The standard of care is handwashing with soap and water, scrubbing hands for at least 20 seconds. The use of alcohol-based hand sanitizer (ABHS) with at least 60% alcohol content is another hand hygiene method that can mitigate COVID-19. Knowledge about appropriate technique and situations to use each method varies, as does personal preference. However, there is a knowledge gap about whether provision of hand hygiene resources leads to increasing reported hand hygiene practices, especially in low- and middle-income countries, and this setting is key to mitigating household transmission of COVID-19.

## Goal, Objectives, and Activities

### Goal

To support the SESAL of Honduras to mitigate the impact of the COVID-19 pandemic by reducing morbidity and mortality among COVID-19 patients managed through existing home-based care strategies with signs and/or diminished blood oxygen level, and by preventing the spread of SARS-CoV-2 to household contacts of patients being managed in this setting.

### Objectives

- 1) To support and strengthen existing HBC for higher risk COVID-19 patients in Honduras
- 2) To generate operationally relevant data to provide the Honduras SESAL and other health authorities with HBC guidance and protocols.
- 3) To assess the utility and impact of pulse oximetry on outcomes for HBC.
- 4) To evaluate differences in resource utilization by HBC strategy.
- 5) To assess acceptability of different HBC strategies by patients, study staff, and SESAL clinicians staffing triage centers.
- 6) To assess the prevalence of post COVID-19 conditions.
- 7) To assess participant-reported in-home hand hygiene practices before and after receiving HBC kit.
- 8) To assess if participants with access to alcohol-based hand sanitizer (ABHS) practice hand hygiene more frequently.
- 9) To evaluate preferences for different hand hygiene technologies.

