## Home-based care kits and strategies

All study participants will receive COVID-19 HBC kits that include soap, face coverings, information sheets on COVID-19 prevention, and other supplies. Half the COVID-19 home kits will include a two-week supply of ABHS. Study participants will be block randomized into ABHS or no ABHS groups according to the day of the week they are tested for COVID-19. Patients assigned to Strategy 2 will be supplied with a portable pulse oximeter and trained on use and measurement by study staff prior to discharge from the triage center. All patients will be asked to return the portable pulse-oximeter when they are discharged from the study. Upon return of the portable pulse-oximeter at the end of the monitoring period, these patients may receive a phone card or similar item of approximately \$10 value to help defray the costs of transportation. Patients who are triaged to HBC but are deemed ineligible for study enrollment may also be provided with an HBC kit if resources are available.

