## Data collection and survey tools

### 1. Enrollment questionnaire

All enrolled patients will complete an enrollment questionnaire that will include demographic and clinical information, risk factors, hand hygiene practices and other WASH variables, and socio-behavioral questions.

Questions will include timing and nature of symptoms, and COVID-19 compatible symptoms, if anyone else in the household has had COVID-19 symptoms in the past 30 days, and if so, when they began and how long they lasted. In order to later link patients with COVID testing results and follow-up visits to the CETTE or hospital in a SESAL database, we will also collect the patient's national identification number, but a unique study identification number will also be assigned. The enrollment questionnaire will also assess risk factors of the participant and household members such as which household members leave the house for work or school and if there are any other possible exposures to COVID-19. Specific questions about the WASH component include assessing the participants' knowledge, attitudes, and practices about hand hygiene in the month prior to visiting the triage center. The enrollment questionnaire will assess access to hand hygiene resources in the participants' homes. The estimated time to complete enrollment and questionnaire is 20-25 minutes.

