## Indicators

Specific indicators will be used to assess the feasibility, impact and acceptance of the HBC intervention. Primary outcome indicators are designated with “\*”. Although final indicators may be updated and/or modified, the preliminary set of indicators are listed below.

- Feasibility
  - o Proportion that receive the prescribed HBC intervention
  - o Proportion with complete pulse oximetry data, for relevant arm
  - o Proportion lost to follow-up
- Referral to higher level of care
  - o Proportion referred to higher level care due to hypoxia (i.e. SpO2 < 92%)
  - o Proportion referred to higher level care due to alarm symptoms
  - o Proportion referred to higher level care for any other reason
  - o Proportion referred that reach higher level of care within 24 hours
  - o Proportion who successfully complete HBC without requiring referral
  - o Disposition after referral (home, admission, other) \*
  - o SpO2 level upon arrival to higher level of care
  - o Other clinical measures upon arrival to higher level of care
- Impact on patient outcomes:
  - o Duration of hospitalization (days)\*
  - o Duration of ICU and/or ventilator requirement\*
  - o Mortality\*
- Acceptability
  - o Perception of utility/benefit of strategy (study staff/patients)
  - o Perception of ease of implementation of strategy (study staff)
  - o Changes in hand hygiene behavior

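### Objective 7's before-after change in hand hygiene cannot be attributed to the kit; it should be labelled descriptive, and any claim about providing resources should rest on the sanitizer versus no-sanitizer contrast

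*Protocol*

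**What the plan says.** The Background section of the protocol names a "knowledge gap about whether provision of hand hygiene resources leads to increasing reported hand hygiene practices". Two objectives bear on it. Objective 7 is "To assess participant-reported in-home hand hygiene practices before and after receiving HBC kit". Objective 8 is "To assess if participants with access to alcohol-based hand sanitizer (ABHS) practice hand hygiene more frequently".

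The section *Home-based care kits and strategies* sets out the contents: "All study participants will receive COVID-19 HBC kits that include soap, face coverings, information sheets on COVID-19 prevention, and other supplies". In addition, half of the kits hold a two-week supply of ABHS, and "Study participants will be block randomized into ABHS or no ABHS groups according to the day of the week they are tested for COVID-19".

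The enrollment questionnaire covers "knowledge, attitudes, and practices about hand hygiene in the month prior to visiting the triage center". The follow-up hand hygiene assessment repeats the practice questions by phone, weekly and at discharge from acute monitoring.

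The only hand-hygiene entry under *Indicators* is "Changes in hand hygiene behavior". It stands under Acceptability and is not starred as primary. *Data analysis* promises unadjusted and adjusted differences between arms, using the covariates listed. The only covariate table, at the end of the sample size section, holds hospitalization, its duration and SpO2 on evaluation at a higher level of care. It has no hand-hygiene item.

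**The concern.** The Background asks a causal question about providing resources. Objective 7 and the change indicator look like the answer to it, since the kit is the event that divides before from after. But no group goes without a kit, and the two time points differ in much more than the kit. If the change were reported as the kit's doing, that reading could enter the home-care guidance that Objective 2 promises to the health authorities.

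The error could run either way. More time at home after a positive test can raise in-home hand hygiene, or raise the reporting of it, with no help from the kit. Illness can also lower practice and hide a real benefit.

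**Working it through.** **Step 1. What differs between the two time points (Protocol).**

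| Feature | Before | After | Part of the kit? |
|---|---|---|---|
| Soap, face coverings, information sheets | not yet supplied | supplied to all | yes |
| Period asked about | the month up to the triage visit | acute monitoring at home | no |
| Infection status | before the study's rapid antigen test | confirmed positive | no |
| Setting of the interview | enrollment at the screening location | phone call | no |
| Staff contact | none yet | daily calls, with the same items asked again | no |

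The information sheets come in the kit, so any effect they have is a kit effect and they are not counted as a rival explanation. The other rows are rival explanations.

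**Step 2. What the change estimates.** In SDs of the within-person change:

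mean change = kit effect + non-kit shift.

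With no group lacking the kit, the two terms cannot be separated. A kit effect of +0.10 with a shift of −0.10 gives a mean change of 0; a kit effect of 0 with a shift of +0.10 gives +0.10. Read as a kit effect, the change would be wrong in both cases.

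**Step 3. Illustration of size.** The protocol gives no test, effect size, SD or sample size for hand hygiene, so there is no planned figure to reproduce. Assumptions: kit effect zero; non-kit shift *s* in SDs of the change; two-sided 5% paired test. The totals 850, 1,608 and 1,892 come from the protocol's calculations for SpO2, referral and hospitalization and serve only as a scale.

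P(reject) = Φ(s√n − 1.96) + Φ(−s√n − 1.96)

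Example: n = 1,892 and s = 0.05 give s√n = 0.05 × 43.50 = 2.17, and Φ(0.21) is about 0.585.

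| Assumed shift *s* | n = 850 | n = 1,608 | n = 1,892 |
|---|---|---|---|
| 0 | 5.0% | 5.0% | 5.0% |
| 0.03 | 14.1% | 22.5% | 25.7% |
| 0.05 | 30.8% | 51.8% | 58.5% |
| 0.10 | 83.0% | 98.0% | 99.2% |

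The formula is symmetric in *s*: a shift of −0.05 gives the same rates, with practice apparently falling.

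**Step 4. The contrast the design already offers.** A shift common to both ABHS groups cancels in their difference. The smallest difference detectable with 80% power is (1.96 + 0.84) × √(2/n per group), in SDs of the change score:

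- 425 per group: 2.80 × √(2/425) = 0.19
- 804 per group: 2.80 × √(2/804) = 0.14
- 946 per group: 2.80 × √(2/946) = 0.13

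These figures treat participants as independently allocated. ABHS is allocated by day of the week, so variation between days would make the contrast less precise, and it could be biased if the days differ systematically.

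**The case against.** The strongest reply is that the protocol never makes the causal claim. Objective 7 only says that practices will be assessed before and after. The indicator is an unstarred Acceptability item in a list called preliminary. No paired test is specified, and the stated primary analysis compares arms. Objective 8, with concurrent ABHS allocation, already gives a between-group answer. Labels and baseline adjustment could also be left to a statistical analysis plan.

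Most of this stands, and it limits the point. A reader might infer that the whole hand-hygiene evaluation lacks a comparator; Objective 8 shows that it does not. A reader might also infer that the evaluation is bound to show a change even if the kit does nothing. The documents do not support that: they give neither the size nor the direction of any non-kit shift, and with no shift the test rejects only 5% of the time. The paired test and every value of *s* are assumptions of this review.

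Two things survive. The Background's question concerns providing resources, while the only hand-hygiene indicator is a change, and nothing in the protocol says that this change is descriptive. And the covariates that the protocol lists for adjustment do not include the enrollment hand-hygiene answer, although it is collected. The objection also rightly warns against overselling the ABHS contrast, given how ABHS is allocated.

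**Conclusion.** The point holds in a limited form. The Objective 7 change, and the matching indicator if read as a simple change over time, mix any kit effect with the effects of diagnosis, time at home and reporting. They cannot show whether providing resources alters practice. This follows from the design and needs no assumed numbers. The rejection rates only illustrate that, at the enrollments the protocol mentions, a shift of 0.05 to 0.10 SD would often reach significance.

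The design does support a claim about adding ABHS to a kit that already contains soap, subject to the day-of-week allocation. It supports none about the kit as a whole. Severity is minor: the component is not primary and a concurrent comparison is already planned.

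**What to change.** 1. In Objective 7 and beside the hand-hygiene indicator, state that the before-after change describes the course from the month before triage to home care during illness, and is not an estimate of the kit's effect.
2. In *Data analysis*, state that any conclusion about providing resources rests on the Objective 8 contrast at follow-up, kit with ABHS versus kit without, adjusted for the participant's enrollment answer to the same item. Limit the conclusion to adding ABHS to a soap kit.
3. Say how the day-of-week allocation is handled. The protocol does not say whether a given weekday keeps the same assignment throughout. If assignments rotate, the analysis can account for the day of testing. If they are fixed, weekday and ABHS cannot be separated, and the report should say so.

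The cost is a few sentences. Enrollment and follow-up answers are already collected, so no new data are needed. The downside is that the trial gives up any claim about the effect of the whole kit.

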### Activities

- 1) Screening of suspected COVID-19 patients
- 2) Confirmation of COVID-19 using rapid SARS-CoV-2 Antigen testing.
- 3) Enrollment of eligible patients into one of the two HBC strategies.
- 4) Administration of enrollment questionnaire to collect data on demographics, clinical variables, medical history, risk factors, and patient-reported in-home hand hygiene practices.
- 5) Provision of COVID-19 HBC kits to all study participants, with and without alcohol-based hand sanitizer.
- 6) Daily phone-based or clinical monitoring of HBC patients, with referral of patients reporting warning signs, according to the national guidelines, to a higher level of care.
- 7) Chart review of study participants referred to a higher level of care to assess clinical features and outcomes.
- 8) Administration of serial phone-based questionnaires to study participants, including at discharge from HBC daily monitoring, to assess acceptability of HBC strategy, participant-reported in-home hand hygiene practices, and other WASH and socio-behavioral parameters.
- 9) Administration of questionnaires to study staff, triage center staff, and other relevant stakeholders to assess acceptability of various HBC strategies.
- 10) Administration of qualitative interviews to a small subset of patients to understand their hand hygiene practices, with and without ABHS.
- 11) Longitudinal serial phone-based questionnaires to assess incidence and temporal features of COVID-19 compatible symptoms among study participants, with referral for medical evaluation as needed.

## Project overview

### Rationale

This project is intended to enhance the existing SESAL HBC approach by providing additional resources and monitoring for patients with confirmed COVID-19 that are discharged home after diagnosis. In addition, given limited data on which home-based care strategies most effectively and efficiently minimize poor outcomes, we aim to monitor two discrete home-based care approaches, daily phone calls from nurses to assess the patient's clinical status, with and without the use of pulse oximeters by patients at home. Assignment to home-based care approach will be randomized. Given the primary goal of the project is to reduce morbidity and mortality due to the COVID-19 pandemic, we will not include a control arm.

### Setting

The project location will be in existing SESAL triage centers, and other COVID screening locations, in the Municipalities of the Central District of Honduras (Tegucigalpa and Comayagua). Selection of target **COVID screening locations** will be performed in collaboration with the Honduras SESAL and based on criteria including current and projected COVID-19 hotspots, mortality data and logistical considerations including access and security. Depending on patient enrollment and other considerations, other health facility types and locations may be included for enrollment.

### Project Population

The study population is patients  $\geq 45$  years old with confirmed COVID-19 assessed to be higher-risk for poor outcomes but clinically stable and suitable for home-based care according to existing Honduras SESAL COVID-19 protocols. The assessment of which patients will be discharged to home will be conducted by SESAL clinicians according to existing SESAL protocols.

### Inclusion and Exclusion Criteria

Inclusion criteria:

- Acute infection with SARS-CoV-2 confirmed by rapid antigen test.
- Patients triaged to HBC by SESAL clinicians according to existing SESAL policies and protocols.
- **45-59 years of age with at least one comorbidity related to increased risk for poor outcomes due to COVID-19 or 60+ years of age.**
- Live or work in the city where the study is being implemented
- Agrees to participate and signs informed consent

Exclusion criteria:

- Negative for SARS-CoV-2 by rapid antigen test
- Patients not triaged to HBC by SESAL clinicians
- Less than 45 years of age, or 45 - 59 years without any comorbid conditions that increase the risk for poor outcomes due to COVID-19
- Does not live or work in the city where the study is being implemented
- Difficulty giving consent to participate due to a medical condition at the time of enrollment

Patients that do not meet all the inclusion criteria above will be excluded from project enrollment.

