## Recruitment procedures

Screening and recruitment will occur at the COVID screening locations. Patients that are evaluated by SESAL clinicians and triaged to HBC will undergo further screening by project staff to assess if they meet project inclusion criteria. Those that (i) are triaged to HBC by SESAL clinicians and (ii) meet the additional project inclusion criteria will be tested for SARS-CoV-2 via rapid antigen test. Those that receive positive test results will be offered enrollment by study staff.

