## Home-based care strategies

At the time of enrollment, participants will be assigned to one of the two following home-based care strategies using a block randomization approach, based on day of presentation to the triage center:

- Strategy 1: Study staff will perform daily phone-based assessments using standardized electronic study tools (tablets). Clinical features will be documented on a phone-based patient monitoring form.
- Strategy 2: Study staff will perform daily phone-based assessments using standardized electronic study tools (tablets). Clinical features and oxygen saturation levels will be documented on a phone-based patient monitoring form. Patients will be provided with a portable pulse oximeter for home use ("MIGHTYSAT" manufactured by MASIMO) or other device certified by the US Food and Drug Administration or European CE). Oxygen saturation level will be assessed up to four times per day (morning, midday, evening, plus during the phone-based assessment) by the patient and/or family member and the lowest stable (i.e. without substantial fluctuations) level recorded during a monitoring period of one minute will be recorded and registered. Patients will be provided monitoring sheets to record the times and dates of the oxygen saturation levels.

Study staff performing patient evaluations and monitoring will be doctors or nurses.

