## Discharge from daily clinical monitoring

All patients will receive daily monitoring until they are discharged from the daily monitoring program.

Criteria for discharge are:

1. Ten days post-symptoms onset and 24 hours without fever. Patients meeting these criteria will be discharged from the daily monitoring program. If a patient continues to experience fever more than 10-days post-symptoms onset they will continue to receive daily monitoring until they are fever-free for more than 24 hours.
- OR
2. Patient is hospitalized. Patients that are not hospitalized will continue in the daily monitoring program until criterion #1 is met.

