#### **4. Follow-up hand hygiene assessment**

Serial follow-up WASH survey will be administered every week and at discharge (from acute COVID-19 daily monitoring) during the daily follow-up phone calls for the HBC study. The follow-up hand hygiene assessment will repeat questions about participant-reported in-home hand hygiene practices. The follow-up questionnaire may also assess the safe usage of the ABHS in the home by asking if there have been any adverse events (e.g. splash in eye or ingestion). This questionnaire is estimated to take 5 minutes. Additionally, to understand behavioral and preferential aspects of different hand hygiene technologies, upon discharge from the period of acute monitoring, 10 patients from each ABHS arm will be selected to complete Hand-Hygiene In-depth Interviews which are estimated to take 5-10 minutes. All patients enrolled in the study are eligible for selection for interviews. The 10 patients will be selected as a convenience sample based on availability of study staff.

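### Eligibility ignores time since symptom onset, but daily monitoring ends on a clock that starts at onset, so some randomised patients can receive little or none of their assigned strategy

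*Protocol*

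**What the plan says.** **Entry.** Protocol, Inclusion and Exclusion Criteria, lists five conditions. The two that bear on disease state are "Acute infection with SARS-CoV-2 confirmed by rapid antigen test" and "Patients triaged to HBC by SESAL clinicians according to existing SESAL policies and protocols". The others cover age with comorbidity, living or working in the study city, and consent. Neither list sets a maximum time since onset or requires symptoms.

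**Recruitment.** Recruitment procedures adds no onset check: "Those that receive positive test results will be offered enrollment by study staff".

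**Assignment.** Home-based care strategies assigns the arm at enrolment. Both arms get daily calls, and Strategy 2 adds home oximetry with readings up to four times a day.

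**End of monitoring.** Discharge from daily clinical monitoring gives criterion 1 as "Ten days post-symptoms onset and 24 hours without fever". Persistent fever extends monitoring past day 10. Criterion 2 is hospitalisation, and everyone else stays until criterion 1 is met.

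**Data already planned.** The enrollment questionnaire (Data collection and survey tools, item 1) records when symptoms began, but eligibility does not use it.

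**The concern.** Entry is open to any day of illness, while the end of the intervention is tied to the day of onset. The intervention period is whatever remains between the two, and nothing in the Protocol keeps it above zero.

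The arms differ only by oximetry during monitoring. A participant with no monitored days counts in the denominator of an arm but carries no contrast between the strategies. Objective 3, the utility and impact of pulse oximetry, would then be tested against a diluted difference.

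There is a second mismatch with the same origin. Criterion 1 counts from symptom onset, and an antigen-positive patient without symptoms has no onset date. As written, such a patient has no defined exit from monitoring other than hospitalisation. That leaves the duration undefined rather than short.

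**Working it through.** **Step 1: monitored days.** For a patient who is afebrile and not hospitalised, enrolled d days after onset:

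monitored days = max(0, 10 − d)

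| d at enrolment | 0 | 3 | 5 | 7 | 8 | 9 | 10 or more |
|---|---|---|---|---|---|---|---|
| monitored days | 10 | 7 | 5 | 3 | 2 | 1 | 0 |

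At d of 10 or more, with 24 hours free of fever and a positive antigen test, a patient can satisfy all the entry conditions and criterion 1 together. A febrile late presenter is still monitored, so the table does not apply to that patient.

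**Step 2: reproduce the plan's figure.** Inputs from Sample size for primary outcome indicators: two-sided alpha 0.05, power 0.80, referral 20% with a 6-point difference (20% versus 26%), 804 per arm. The two-proportion formula with pooled variance under the null gives 772 per arm without continuity correction and 805 with it (804.05 before rounding up). The plan's 804 is therefore the continuity-corrected figure, and the correction is kept below.

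**Step 3: dilution, as an illustration.** Let f be the share of participants with no exposure. The documents give no distribution of time from onset to enrolment, so f is an assumption. Two versions are shown:

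- A: unexposed patients keep the 20% referral risk in both arms, so the arms are 20% and 20% + 6(1 − f) points.
- B: unexposed patients are also past the risk of referral, so the arms are 20%(1 − f) and 26%(1 − f).

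In both, the difference is δ = 0.06(1 − f). With n = 804 and p̄ the mean of p1 and p2:

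- n₀ = n(1 − 1/(nδ))²
- power = Φ{[δ√n₀ − 1.96√(2p̄(1 − p̄))] / √(p1(1 − p1) + p2(1 − p2))}

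Worked for f = 10%, version A: δ = 0.054; n₀ = 804(1 − 1/43.416)² = 767.4; δ√n₀ = 1.496; p̄ = 0.227, so the null term is 1.96 × 0.5924 = 1.161; the denominator is 0.591. Power = Φ(0.335/0.591) = Φ(0.566) = 0.71.

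| f | A: arms | A: power | B: arms | B: power |
|---|---|---|---|---|
| 0 | 20% v 26% | 0.80 | 20% v 26% | 0.80 |
| 2% | 20% v 25.9% | 0.78 | 19.6% v 25.5% | 0.79 |
| 5% | 20% v 25.7% | 0.76 | 19.0% v 24.7% | 0.77 |
| 10% | 20% v 25.4% | 0.71 | 18.0% v 23.4% | 0.74 |
| 20% | 20% v 24.8% | 0.61 | 16.0% v 20.8% | 0.68 |

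Participants with only a few monitored days are counted here as fully exposed.

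**The case against.** **The affected group may be tiny.** Zero exposure needs a patient at least ten days from onset, afebrile for 24 hours, still antigen positive, and triaged to home care. The criterion says acute, Activities refers to screening suspected patients, and the national triage rules, which are not reproduced, may screen out late or symptom-free cases. This stands as to frequency. It does not remove the mismatch, because none of these is a day limit stated in the Protocol, and Setting allows other screening locations and facility types.

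**Broad entry suits an operational evaluation.** Late presenters are people the health service does send home, and Data analysis plans a subgroup analysis by timing of the interventions. The argument has force against a tight onset cap. It has little force for someone who is dischargeable at the moment of randomisation, and a subgroup analysis cannot recover enrolment spent on that person.

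**The power illustration can be challenged.** The 6 points are not described as a full-exposure effect. Referral proportion carries no primary-outcome mark under Indicators, although it has an entry in the primary-outcome sample size section. That section also gives 946 per arm for hospitalisation. If 946 governed, power for referral would be 0.86 with no dilution and 0.79 (version A) or 0.81 (version B) at f = 10%. These points stand, so the figures show direction and scale only.

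**Stronger readings that the text does not support.**

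- A reader might infer that the comparison is biased. Late presenters fall in both arms, so the effect of this feature alone is dilution.
- A reader might infer that the hand hygiene follow-up is lost for anyone enrolled more than three days after onset. An afebrile patient of that kind would miss the first weekly survey, but the plan also surveys at discharge, so a before-and-after comparison remains.
- A reader might infer that patients without symptoms receive too little monitoring. For them the end is undefined, which is a different gap.

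**Conclusion.** The eligibility and discharge sections do not fit together. Entry has no onset limit and monitoring has no minimum length, so an afebrile patient at day 10 or later can be randomised to a strategy that is already over. For a patient without symptoms, criterion 1 cannot be applied at all. Both statements follow from the text and need no assumption.

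The size of the effect cannot be determined from the documents. Under the stated assumptions, the loss of power for referral at 804 per arm is 1 to 2 percentage points if 2% of participants are unexposed, 3 to 4 points at 5%, 6 to 9 points at 10% and 12 to 19 points at 20%. The smaller loss in each pair assumes that late presenters are also past the risk of referral. The correction is worth making because it is cheap, not because a large loss has been shown.

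**What to change.** Reconcile Inclusion and Exclusion Criteria with Discharge from daily clinical monitoring in two places:

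1. Add an exclusion from randomisation for patients who already meet discharge criterion 1 at enrolment. Symptom timing is already in the enrollment questionnaire; it needs to be asked, with fever in the previous 24 hours, before assignment rather than after.
2. State how criterion 1 applies to patients without symptoms, or state that they are not eligible. The choice is the sponsor's.

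Whether to add a further cap on days since onset, and at what number, is also for the sponsor. The documents give no basis for a particular value, and a tighter cap trades recruitment and applicability for more monitored days per participant.

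The cost is an amendment of a few lines and a small loss from the recruitment pool. The patients lost add nothing to the contrast between strategies, and Home-based care kits and strategies already allows ineligible patients to be given a kit if resources permit.
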